#### SDT training

To promote participants’ autonomy, instructors will give meaningful rationale for the activities and exercises used in the intervention, directions will be presented in a non-pressuring manner (e.g., “you could” versus “you should”), instructors will tailor the class to the participants’ needs and abilities so that they will experience an optimal level of challenge, and will give students choice regarding the difficulty and types of exercise used within the class [37, 58]. In order to promote participants’ sense of competence, instructors will provide participants with clear instructions during the intervention, and they will provide positive feedback when participants enact the desired behaviors [37, 58]. To satisfy participants’ relatedness needs, instructors will encourage positive relationships within the intervention setting by perspective taking, by noting verbal and non-verbal cues that indicate how participants feel during the intervention, and by working within participants’ comfort zones in order to make the intervention an interesting and rewarding experience [37, 58].

Additionally, the experimenter will meet with the exercise instructors in the intervention groups four times for half an hour during the intervention to discuss their use of SDT and MI techniques and to have them engage in a few role play exercises to strengthen certain skills. To increase the amount of practice that the instructors have using SDT and MI in the current study, the intervention exercise instructors will be encouraged to utilize these techniques within their other exercise classes and within their daily life. The experimenter will not meet with the exercise instructors in the control group during the intervention.

### Treatment fidelity assessment

Treatment fidelity will be assessed in order to determine whether the intervention is implemented as intended and whether the intervention groups differ from the control groups in terms of their use of SDT and MI techniques. Therefore, an audio recording will be created for each exercise instructor before they are trained in SDT and MI. These recordings will be used to determine the percent of MI- and SDT-adherent components that the exercise instructors demonstrated at baseline. An audio recording will also be created for all of the intervention sessions, which will be coded every fourth week as the intervention progresses. The sessions will be coded by the experimenter (who will not be blind to condition) and a research assistant (who will be blind to condition). High inter-rater reliability will provide evidence of agreement in use of the coding technique by both coders. This information will be coded in order to allow the experimenter to assess treatment fidelity at the different sites. Deviations from SDT and MI techniques will be identified and reviewed with the exercise instructors. The Motivational Interviewing Treatment Integrity Code (MITI) version 3.1.1 [59] will be used to assess the fidelity of the motivational interviewing components of the intervention, as well as participants’ language use within the sessions. Exercise instructors’ use of MI will also be assessed by the Client Evaluation of Motivational Interviewing Scale [60]. A self-created measure based on Wilson, Griffin, Saunders, Kitzman-Ulrich, Meyers, & Mansard [61] will be used to assess the fidelity of the SDT components of the intervention.

### Measures

Participants will complete a number of surveys during pre-intervention, session 4, session 8, and session 12. All of the data will be collected, entered into the computer, and maintained by the experimenter. A description of the primary and secondary outcome measures are listed below, as well as the measures used to assess treatment fidelity.

### Primary outcome measures

#### Physical activity

Physical activity will be assessed using the YMCA’s records of how often the participant came to the control or intervention class (as a measure of persistence), how often the participant attends the YMCA during the intervention and 6 months following the intervention (as a measure of adherence post-intervention). Physical activity will also be assessed using two self-report measures: one question to assess muscle-strengthening exercise from the Behavioral Risk Factor Surveillance System Questionnaire [62], as well as using the long and short version of the International Physical Activity Questionnaire (IPAQ) [63]. The IPAQ weights the frequency of strenuous, moderate and low intensity physical activity by its metabolic equivalent, which quantifies the energy expenditure in each level of physical activity based on its intensity.

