### Hypotheses for secondary outcomes: need fulfillment, well-being, adherence

*Hypothesis 2A*. Participants in the intervention groups will experience a greater increase in need fulfillment, psychological well-being, and physical activity adherence than participants in the control groups (i.e., a significant main effect of condition).

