#### Participants recruited

Participants were recruited using online advertisements (YMCA Facebook website) and hard-copy advertisements that were displayed at the YMCA and throughout the city of Syracuse at public libraries, community centers, churches, etc. If the YMCA members were interested in participating, they completed a survey online through Qualtrics or a hard copy version of the survey in order to determine whether they were eligible to participate in the study. The inclusion criteria mandated that participants were currently healthy enough to exercise once a week, not be pregnant or planning to get pregnant within the next 3 months, were willing to attend an exercise class once a week for 12 weeks, were willing to complete questionnaires at baseline and 12 weeks, allowed the intervention staff to monitor their attendance at the YMCA for 6 months post intervention, and allowed the exercise instructor to create an audio recording of all of the intervention sessions.

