### Planned statistical analyses

The analysis plan involves a 2 (race/ethnicity) × 2 (condition: intervention vs. control) factorial ANCOVA with pretest scores entered as covariates to test Hypotheses 1A-1C involving physical activity (assessed by the International Physical Activity Questionnaire [63]). Analysis of variance will be used to test Hypothesis 2A involving need fulfillment (assessed by the Basic Psychological Needs in Exercise Scale [65] and the Behavioural Regulation in Exercise Questionnaire [66]), physical activity adherence (assessed by how often participants attend the YMCA six months post-intervention), and psychological well-being (assessed by the Psychological General Well-being Index [64]). When examining whether mediators account for the relationship between intervention condition and physical activity, the Preacher and Hayes [69] nonparametric bootstrap approach will be used (i.e., Hypothesis 1D using the Basic Psychological Needs in Exercise Scale [65] and the Behavioural Regulation in Exercise Questionnaire [66] and Hypothesis 1E assessed by the Client Evaluation of Motivational Interviewing Scale [60]).

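### The adherence part of Hypothesis 2A predicts an increase in YMCA attendance, but no attendance before the intervention is recorded, so only a post-intervention difference between arms can be estimated

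*Protocol article*

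**What the plan says.** All references are to the protocol article.

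- **Hypotheses for secondary outcomes.** Hypothesis 2A reads "Participants in the intervention groups will experience a greater increase in need fulfillment, psychological well-being, and physical activity adherence" than the control groups. It adds that this would appear as a main effect of condition.
- **Physical activity (under Primary outcome measures).** The attendance record covers "how often the participant attends the YMCA during the intervention and 6 months following the intervention (as a measure of adherence post-intervention". No earlier window is named.
- **Planned statistical analyses.** The adherence variable is "physical activity adherence (assessed by how often participants attend the YMCA six months post-intervention"; I read this as visits over the 6 months after the programme. The method is given as "Analysis of variance will be used to test Hypothesis 2A involving need fulfillment" and the other 2A outcomes, with no pretest covariate mentioned. The IPAQ analysis, in contrast, is a "factorial ANCOVA with pretest scores entered as covariates to test Hypotheses 1A-1C involving physical activity".
- **Participants recruited.** Participants had to have "allowed the intervention staff to monitor their attendance at the YMCA for 6 months post intervention". Nothing is said about looking back at earlier records. The same section speaks of YMCA members ("If the YMCA members were interested in participating"), but it also says that advertisements were placed at libraries, community centres and churches.
- **Table 2, footnote.** The listed pre- and post-test survey contains the support, needs, regulation and well-being scales. It has no item on YMCA visits.

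**The concern.** An increase needs a starting value. For adherence, the hypothesis names a change, while the data source and the analysis variable supply only a value after the programme. A report could then state that adherence increased when nobody measured where it began.

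The point has some weight because YMCA attendance is the only record-based outcome in the planned analyses. It is also the only one followed for 6 months, and the Discussion concedes that the primary outcome is self-reported. Earlier visiting plausibly predicts later visiting. A small trial that leaves such a predictor unused gives up precision on the one outcome that does not depend on recall.

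**Working it through.** **1. Which parts of 2A have a starting value?**

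| 2A outcome | Before or at session 1 | Later value | Change can be formed? |
|---|---|---|---|
| Need fulfilment (needs and regulation scales) | Pre-test survey | Session 12 | Yes |
| Psychological well-being | Pre-test survey | Session 12 | Yes |
| Adherence (YMCA visits) | None described | 6 months after | No |

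Visits during the 12 weeks cannot fill the gap. They come after randomisation, include the assigned classes, and may themselves be affected by condition.

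**2. What does the post-only contrast estimate?** Let A0 be visits before the programme and A1 visits after it. Randomisation gives both arms the same expected A0. The expected difference in A1 therefore equals the expected difference in A1 − A0, and the comparison is unbiased. What it cannot show is the direction of change within an arm. If attendance fell in both arms, but less under the intervention, the contrast would look the same as if it had risen in both.

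**3. How large is a chance imbalance in prior visits?** Table 1 gives arms of 27 and 30.

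- SD of the between-arm difference in mean prior visits: √(1/27 + 1/30) = √(0.0370 + 0.0333) = 0.265 SD.
- With correlation r between prior and later visits, a one-SD imbalance shifts the adherence contrast by r × 0.265. That is 0.11 SD at r = 0.4 and 0.19 SD at r = 0.7.
- The expected shift is zero, and the standard error of the post-only comparison already contains it.

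**4. What would a baseline count gain?** The variance of each analysis relative to post-only is 2(1 − r) for a change score and 1 − r² for covariate adjustment. The standard error with the covariate is 0.265 × √(1 − r²). The article gives no value of r; the range is assumed.

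| r (assumed) | Change score | Covariate | SE with covariate (post-only 0.265) |
|---|---|---|---|
| 0.3 | 1.40 | 0.91 | 0.253 |
| 0.4 | 1.20 | 0.84 | 0.243 |
| 0.5 | 1.00 | 0.75 | 0.230 |
| 0.7 | 0.60 | 0.51 | 0.189 |

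Over r = 0.4 to 0.7 the covariate removes 16% to 49% of the residual variance. A change score is less precise than the post-only comparison when r is below 0.5. A prior count is therefore better used as a covariate than subtracted.

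**5. The plan's own figure.** The article gives no figure for adherence. Its sample size of 48 (f = 0.50, alpha 0.05, power 0.80) is reproduced by an F test with 3 numerator degrees of freedom and four groups, with power 0.803. This point does not change it.

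**The case against.** The strongest reply is that nothing is wrong with the comparison. Participants were randomised within site and race/ethnicity stratum, and the control arm is what separates the intervention effect from prior habit. Hypothesis 2A itself equates its prediction with a main effect of condition. The outcome section calls the record a post-intervention measure, so a reader can tell what will be compared. One verb serves three outcomes and is loose for the third. This reply largely stands, and it confines the defect to wording and precision.

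Other parts of the reply also have force. A shift of 0.11 to 0.19 SD is modest beside the planning effect of f = 0.50, which is d = 1.0 for two equal groups. Prior activity is not wholly unmeasured, because the IPAQ analysis already requires a pretest score. Recruitment reached beyond the YMCA, so the share of participants with a visit history is unknown.

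It might also be said that a journal article leaves such details to a fuller document. That does not answer the point. The article itself fixes the collection window and the analysis variable, and these do not match its own hypothesis.

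Two stronger readings are tempting. A reader might infer that prior habit biases the adherence result. The randomised design does not support that: chance imbalance is part of sampling error. A reader might also infer that every participant was an existing member with past visits on file. The recruitment section does not establish that either.

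**Conclusion.** The mismatch is real and limited. For this secondary outcome the plan states an increase but provides for neither a change nor a contrast adjusted for earlier attendance. The ANOVA remains a valid test of whether post-intervention attendance is higher in one arm. It cannot show that attendance rose in either.

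The cost in precision is 16% to 49% of the residual variance if r lies between 0.4 and 0.7, and less if many participants were new members. The calculation treats the 57 in Table 1 as the randomised set, with complete visit records, and treats participants as independent within classes.

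**What to change.** State the adherence part of Hypothesis 2A as a between-arm difference in YMCA attendance over the 6 months after the intervention. This alone removes the contradiction and costs nothing.

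To recover precision, where the YMCA records and permissions allow:

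- Extract each participant's visit count for a fixed window before session 1 from the same record system.
- Enter it as a covariate in the adherence analysis, with an indicator for people who were not yet members. Without the indicator, a zero would mix people who had no access with members who stayed away.
- If it cannot be extracted, use the baseline IPAQ score that the primary analysis already needs. It adjusts for prior activity but does not permit a statement about change in attendance.

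The choice of covariate should be fixed before the post-intervention counts are examined. The cost is one further extraction and a consent and IRB wording change, because the stated permission covers monitoring after the intervention. Participants carry no added burden. The main downside is a weaker covariate if many participants were new members.

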### Secondary outcome measures

#### Psychological well-being

The Psychological General Well-Being Index (PGWBI) will be used as an assessment of psychological health [64]. This 22-item scale assesses individuals’ anxiety (e.g., “Have you been bothered by nervousness or “your nerves” during the past month”), vitality (e.g. “How much energy, pep or vitality did you have or feel during the past month”), depressed mood (e.g., “Have you felt downhearted or blue during the past month), self-control (e.g., “I was emotionally stable and sure of myself during the past month), general health (e.g. “Have you been bothered by any illness, bodily disorder, aches or pains”) and positive well-being (e.g., I felt cheerful, and lighthearted during the past month”). The items are answered on a 6-point scale which ranges from 0 (*None of the time*) to 5 (*All of the time*).

#### Need fulfillment during exercise

The Basic Psychological Needs in Exercise Scale (BSNES) will be used to assess need fulfillment during exercise [65]. This measure is comprised of 11 items and responses are provided on a 5-point Likert scale ranging from 1 (I don’t agree at all) to 5 (I completely agree). This measure assesses participants’ sense of autonomy (e.g., “I feel that the way I exercise is a true expression of who I am”), competence (e.g., “I feel that exercise is an activity that I do very well”), and relatedness (e.g., “My relationships with the people I exercise with are very friendly”).

#### Intrinsic motivation for exercise

Individuals’ motivation for exercise will be assessed using the 15-item Behavioural Regulation in Exercise Questionnaire (BREQ) by Mullan, Markland & Ingledew [66]. This measure includes four subscales, which are external regulation (e.g., “I feel under pressure from my friends/family to exercise”), introjected regulation (e.g., “I feel guilty when I don’t exercise”), identified regulation (It’s important to me to exercise regularly”) and intrinsic regulation (e.g., “I exercise because it’s fun”) in regards to engage in physical activity behavior. The BREQ was selected over the BREQ-2 (a measure which includes four items assessing amotivation) due the fact that the experimenter expected participants to have some motivation to exercise due to the fact that they volunteered to attend a weekly exercise class; hence, it is expected that adding the amotivation subscale would be of little benefit. Although integrated regulation is not included in the BREQ, Wilson, Rodgers, Loitz, and Scime [67] created a 4-item subscale to assess integrated regulation (e.g., “I consider physical activity consistent with my values”) which is meant to be used in conjunction with the BREQ and will be utilized in the current study.

#### Social support for exercise

The Support for Exercise Habits Scale will be used to assess how much social support participants get from their family and friends in regards to their exercise behavior [68]. Participants complete the questionnaire using a five-point scale that ranges from 0 (*none*) to 5 (*very often*). This 30-item scale is comprised of two subscales: participation/involvement (e.g., “Exercised with me”) and rewards/punishments (e.g., “Got angry at me for exercising”).

### Treatment fidelity measures

#### MI techniques

Exercise instructors’ MI proficiency will be assessed at both the instructor-level and at the participant-level. The percentage of MI-adherent responses will be audio recorded using the Motivational Interviewing Treatment Integrity Code (MITI), version 3.1.1 [59]. The experimenter will code every fourth session to detect MI-adherent responses within the language that the exercise instructors use while interacting with participants. Instructors’ MI proficiency will also be assessed by the students in their classes. The Client Evaluation of Motivational Interviewing Scale [60] will be used to assess whether the participants perceive the exercise instructors to be using MI skills every fourth session. This sixteen item scale assesses two subscales: relational and technical factors associated with MI proficiency using a 4 point Likert scale which varies from 1 (never) to 4 (a great deal). An example of the relational factors includes the item, “The exercise instructor changed the topic when I became upset about changing my behavior.” A technical item is, “The exercise instructor helped you talk about changing your behavior.”

### Planned statistical analyses

The analysis plan involves a 2 (race/ethnicity) × 2 (condition: intervention vs. control) factorial ANCOVA with pretest scores entered as covariates to test Hypotheses 1A-1C involving physical activity (assessed by the International Physical Activity Questionnaire [63]). Analysis of variance will be used to test Hypothesis 2A involving need fulfillment (assessed by the Basic Psychological Needs in Exercise Scale [65] and the Behavioural Regulation in Exercise Questionnaire [66]), physical activity adherence (assessed by how often participants attend the YMCA six months post-intervention), and psychological well-being (assessed by the Psychological General Well-being Index [64]). When examining whether mediators account for the relationship between intervention condition and physical activity, the Preacher and Hayes [69] nonparametric bootstrap approach will be used (i.e., Hypothesis 1D using the Basic Psychological Needs in Exercise Scale [65] and the Behavioural Regulation in Exercise Questionnaire [66] and Hypothesis 1E assessed by the Client Evaluation of Motivational Interviewing Scale [60]).

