### Participants

An a priori ANOVA power analysis was conducted to determine how large a sample would be needed to detect significant main effects and interactions (G*Power version 3.1.3., 2010). This was estimated using a large effect size (f = 0.50), an alpha level of 0.05, and the power was estimated at 0.80. This power analysis determined that 48 participants are needed in the sample in order to detect a statistically significant change in an effect of this size.

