### SDT and MI Intervention

All participants will participate in 12 weekly sessions for one hour with a YMCA instructor who has been trained to teach exercise classes. A brief intervention will be utilized because past research suggests that brief interventions based on both SDT and MI can increase participants’ physical activity and physical activity adherence over time [38, 41]. Participants in the intervention groups will engage in group discussions led by an SDT and MI-trained exercise instructor and will engage in exercise. The control groups will be taught by an exercise instructor who will not be trained in SDT and MI. The participants in the control groups will engage in exercise classes that are not based on any clinical or theoretical basis. This is an appropriate comparator since the control sessions closely resemble group exercise classes that are traditionally taught at gyms. Figure 2 shows a timeline for the intervention.

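### The condition tests (1B, 2A) and the sample size assume independent participants, although treatment is given in instructor-led classes nested in arm; the size of the error depends on an unstated number of classes and ICC

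*Protocol article*

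**What the plan says.** Under *Assignment to condition*, individuals choose one of two sites and are then randomised 1:1 within site and minority status. Under *SDT and MI Intervention*, everyone attends 12 weekly one-hour classes. In one arm, "Participants in the intervention groups will engage in group discussions led by an SDT and MI-trained exercise instructor"; in the other, "The control groups will be taught by an exercise instructor who will not be trained in SDT and MI". An instructor, and so a class, therefore belongs to one arm only. *Intervention sessions* adds that instructors choose the topic of two sessions and adapt the programme to their group.

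Under *Planned statistical analyses*, Hypotheses 1A–1C are tested with a "2 (race/ethnicity) × 2 (condition: intervention vs. control) factorial ANCOVA with pretest scores entered as covariates" on the IPAQ, and Hypothesis 2A with analysis of variance. Neither model has a class, instructor or site term.

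Under *Participants*, the sample size is described this way: "An a priori ANOVA power analysis was conducted to determine how large a sample would be needed to detect significant main effects and interactions". Its inputs are: "This was estimated using a large effect size (f = 0.50), an alpha level of 0.05, and the power was estimated at 0.80". The result: "This power analysis determined that 48 participants are needed in the sample". No ICC or design effect enters. *Participants enrolled* reports 57 people (27 intervention, 30 control). The limitations in the *Discussion* do not mention clustering.

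**The concern.** Individual randomisation balances people at entry. It does not remove the correlation that arises afterwards when people share an instructor and a group for 12 weeks. Here the shared elements (group discussion, relationships within the class, the instructor's MI skill) are what the intervention works through, so some within-class correlation is to be expected.

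A person-level ANCOVA on 57 people has 57 − 4 cells − 1 covariate = 52 residual degrees of freedom and takes its error variance from differences between people. If class means also vary within arm, that error term leaves out a component that does not shrink as people are added to a class. The condition test in 1B and 2A then rejects too often when the claim concerns SDT/MI training as such, which is the aim set out in the abstract. A significant result for 1B, the main efficacy hypothesis, could partly reflect which instructors taught in which arm.

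**Working it through.** **Inputs from the article.** f = 0.50 (a 1.0 SD difference for two equal groups), alpha 0.05, power 0.80, required N = 48, enrolled N = 57, two sites with both conditions at each.

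**Assumptions (not in the article).** Number of classes K: both conditions at two sites imply at least 4; I use 4 and 8. ICC: 0.01 to 0.10. Classes are of equal size m = N/K. The 1.0 SD is on the residual scale, so the pretest covariate earns no further credit.

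**Step 1: reproduce 48.** Noncentral F with λ = f²N = 0.25 × 48 = 12.
- Numerator df 3, four groups (error df 44): power 0.803. This reproduces 48.
- Numerator df 1 reaches 0.80 at N = 34, so it does not give 48.

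So 48 is the omnibus figure for four cells under independence, with no hidden allowance for clustering. The 1-df condition test then has nominal power 0.92 at N = 48 and 0.96 at N = 57.

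**Step 2: design effect.** DEFF = 1 + (m − 1) × ICC. For K = 4, N = 57, m = 14.25: at ICC 0.05, 1 + 13.25 × 0.05 = 1.66; at 0.10, 2.33. For K = 8, m = 7.125: 1.31 and 1.61.

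**Step 3: type I error of the unadjusted condition test.** Approximately 2 × [1 − Φ(1.96/√DEFF)]. For K = 4, ICC 0.05: 1.96/√1.6625 = 1.52, giving 0.128. Simulations for four classes agree (about 0.12 to 0.13 at ICC 0.05, 0.20 to 0.21 at 0.10).

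**Step 4: power for the planned effect, two ways.**
- (a) Design effect only, person-level df: noncentral F with λ = 0.25 × N/DEFF on 1 and N − 4 df.
- (b) Class-level inference, which generalises beyond these instructors: noncentral t on K − 2 df with noncentrality 1/√(4 × DEFF/N). For K = 4, ICC 0.05: 1/√(4 × 1.6625/57) = 2.93 on 2 df.

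Results for N = 57:

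| K | ICC | Type I error | Power (a) | Power (b) |
|---|---|---|---|---|
| 4 | 0 | 0.050 | 0.96 | 0.53 |
| 4 | 0.01 | 0.066 | 0.94 | 0.49 |
| 4 | 0.02 | 0.081 | 0.91 | 0.45 |
| 4 | 0.05 | 0.128 | 0.82 | 0.37 |
| 4 | 0.10 | 0.199 | 0.68 | 0.30 |
| 8 | 0 | 0.050 | 0.96 | 0.88 |
| 8 | 0.01 | 0.057 | 0.95 | 0.86 |
| 8 | 0.02 | 0.064 | 0.94 | 0.84 |
| 8 | 0.05 | 0.086 | 0.90 | 0.79 |
| 8 | 0.10 | 0.123 | 0.83 | 0.70 |

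Under (a), N = 57 keeps 0.80 up to an ICC of about 0.06 with 4 classes and 0.12 with 8.

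**Step 5: what four classes can support.** If site is added, as randomisation within site calls for, class-level inference with 4 classes has 1 df and power of about 0.18 at ICC 0.05.

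**The case against.** The strongest reply is about size. The article fixes neither the number of classes nor an ICC. The analysed outcome is self-reported overall activity, much of which can take place outside a one-hour weekly class, so a low ICC is plausible. At ICC 0.01 to 0.02 the type I error is only about 0.06 to 0.08 over the two layouts. This stands: the direction is certain for any positive ICC, but the size is conditional.

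A reader might infer that the trial simply lacks its stated 80% power. The documents do not support that. Because 48 was sized for a 3-df test, the condition test has slack, and even 4 classes at ICC 0.05 keep about 0.82 once the design effect is applied. The low figures in column (b) come mainly from having 2 degrees of freedom: the 0.53 at ICC 0 is the price of class-level inference, since at ICC 0 the planned ANCOVA is valid and has 0.96.

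A reader might also infer that any intervention effect would be merely an instructor difference. That goes too far. *Treatment fidelity assessment* plans a recording of each instructor before SDT/MI training and coding of later sessions, which gives some information on prior skill versus training. It does not correct the standard error.

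Finally, a fuller protocol or analysis plan may say more. The point does not rest on missing detail: the model and the power calculation, as written, assume independence.

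**Conclusion.** The point holds in conditional form. For any positive within-class correlation, the planned condition tests in 1B and 2A are too liberal for a conclusion about SDT/MI training in general. Assuming 57 people in 4 classes, the type I error is about 0.07, 0.08, 0.12–0.13 and 0.20 at ICC 0.01, 0.02, 0.05 and 0.10; assuming 8 classes, about 0.06, 0.06, 0.09 and 0.12.

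The stated 80% power is conditional on independence, and whether it survives depends on the intended reach of the conclusion. With a design effect alone, 4 classes keep 0.82 at ICC 0.05 and fall to 0.68 at 0.10. For a conclusion that reaches beyond these instructors, power at ICC 0.05 is about 0.37 with 4 classes and 0.79 with 8.

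The interaction in 1C is less affected because race/ethnicity varies within classes, although the *Discussion* says that certain classes consist mostly of minority participants, so protection may not be complete.

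**What to change.** - State the number of classes and instructors per arm and site.
- Include site as a fixed effect, since randomisation was within site.
- If there are enough classes per arm, test condition in 1B and 2A with a random intercept for class and Kenward-Roger degrees of freedom, or with covariate-adjusted class means, and report the ICC.
- If there are only about two classes per arm, a random intercept is close to uninformative. Keep the person-level ANCOVA, state that its inference is conditional on these instructors and cannot separate training from instructor, and show the condition result with the standard error inflated by √DEFF over a range of ICCs, for example 0.01 to 0.10.
- Under *Participants*, say that the power assumes independence and give the range under clustering.

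Cost: wider intervals, a less favourable stated power and, with few classes, a narrower conclusion. No new data are needed.
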